### Data points

Data points relating to patient, immunosuppression status, operative method and postoperative period will be collected (table 1). In order to maximise data completeness, a minimal data set has been designed to test only factors relevant to the outcome measures. Investigators will enter data via the secure internet-based Research Electronic Data Capture (REDCap) system.^22^ Anonymous patient data will be held on the system hosted by the University of Edinburgh, Scotland, UK.

**Table 1 T1:** Required data fields

Patient ID	Local hospital field
Age	If >2 years = whole years, if <2 years = months
Gender	Male, female
ASA score	I, II, III, IV, V, not recorded
Immunosuppression	Diabetes: Diet controlled, Tablet controlled, Insulin controlled, No HIV: Yes—on antiretroviral therapy; Yes—not on antiretroviral therapy, No, Unknown Steroids: Yes, No Other immunosuppressive drugs (eg, azathioprine, methotrexate, biologic agents): Yes, No Chemotherapy (current chemotherapy or if the last cycle was within 12 weeks of operation): Yes, No Active malarial infection: Yes—confirmed by blood film or equivalent test, No
	HIV: *Yes*—most recent preoperative CD4 count
Smoking status	Current smoker (including those who stopped smoking within the last 6 weeks), Previous smoker, Never smoked, Unknown
Date and time of admission	DD/MM/YYYY HH:MM
Date and time operation started (knife to skin time)	DD/MM/YYYY HH:MM
Length of operation (knife to skin until point of completion)	Minutes
Urgency of operation	Emergency (any surgery on the same admission as diagnosis), Semielective, Elective (any planned admission for surgery)
Was a surgical safety checklist used (WHO or an equivalent)?	Yes, No—but available in this centre, No—not available in this centre
Initial operative approach	Open midline, Open non-midline, Laparoscopic, Laparoscopic converted to open, Robotic, Robotic converted to open
Primary operation performed	Pick from drop-down list; pick single main procedure performed
	Appendicectomy—Appearance at surgery: simple (non-perforated), complex (perforated, free pus), normal
	Appendicectomy—Duration of symptoms (eg, abdominal pain) prior to surgery (days 0, 1, 2, 3, 4, 5, 6, 7+)
Main surgical pathology/indication (the main cause leading to surgery)	Malignant (proven or suspected tumour/cancer), Benign
Intraoperative contamination	Clean contaminated: GI tract entered but no gross contamination Contaminated: GI tract entered with gross spillage or major break in sterile technique Dirty: There is already contamination prior to operation (eg, with faeces or bile)

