### Statistical analysis and power calculation

Identification of hospital or surgeon-specific performance will not be reported. Variation in outcome across different contexts will be tested using the HDI^24^ (a composite statistic of life expectancy, education and income indices). Following analysis, centre-specific SSI rates will be fed back to participants. Hierarchical logistic regression multivariate analysis will be used to adjust the influence of HDI on SSI rates for confounding patient and disease variables. We will subgroup patients according to operative procedure for the purpose of analysis.

An appropriate sample size is difficult to calculate in this setting as there is a lack of previous study data to indicate the incidence of SSIs internationally. The previous GlobalSurg study recruited 10 745 patients using the same methodology.^25^Although the inclusion criterion for this study is different, we expect to achieve a similar number of patients. Based on the findings from GlobalSurg 1, this number will provide adequate power to show a minimum difference from 7% to 10% in SSI rate between two groups (80% power at 5% alpha requires a sample size of 1350 patients).

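### Trauma is an eligible indication, but the indication field offers only Malignant or Benign, so on the fields shown trauma cases cannot be directly identified or adjusted for (minor)

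*Protocol article*

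**What the plan says.** Three parts of the protocol article bear on this.

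- **Eligibility.** Box 1, under Patient inclusion and exclusion criteria, lists trauma as a primary indication that sites are to include.
- **Coding.** Table 1, under Data points, sets out the required fields. One field captures the pathology or indication, meaning the cause that led to surgery. Its printed options are "Malignant (proven or suspected tumour/cancer), Benign". There is no trauma, other or unknown option, and no sub-field follows Benign. The operation field is a separate item: "Pick from drop-down list; pick single main procedure performed".
- **Analysis.** The Statistical analysis and power calculation section plans hierarchical logistic regression to "adjust the influence of HDI on SSI rates for confounding patient and disease variables". On subgroups it says: "We will subgroup patients according to operative procedure for the purpose of analysis". No subgroup by indication is mentioned.

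**The concern.** The eligibility list names an indication that the indication field has no value for. A bowel resection for injury then carries the same indication code as any other operation not done for cancer.

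This matters for the adjusted HDI comparison. Indication is one of the few disease variables collected. If trauma is commoner in some HDI groups and has its own SSI risk, the Benign category has a different composition in different settings. Some of that case mix would then stay in the HDI estimate. An analysis plan written later could not adjust directly for, or exclude, a category that was never coded. Readers of the results also could not be told how many trauma cases were included.

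**Working it through.** **Step 1. Is there another route to trauma in the fields shown?** I compared Box 1 with the fields of Table 1.

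| Field | Does it identify trauma? |
|---|---|
| Indication | No. Two levels, cancer or not |
| Urgency | No. Shared with all other emergency operations |
| Contamination | No. Shared with perforation and spillage from any cause |
| ASA, operative approach, duration | No. They describe the case, not its cause |
| Operation | It records the procedure; its drop-down list is not reproduced |

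Table 1 prints conditional sub-fields where they exist (CD4 count after HIV; appearance and symptom duration after appendicectomy). None is attached to Benign. On the fields shown, trauma has no identifier.

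**Step 2. How much could this move the HDI estimate?** The plan gives no figure for trauma, so there is none to reproduce and everything here is illustration.

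Assumptions, none from the documents:
- SSI risk without trauma is p0 = 10% in both HDI groups, so there is no true HDI effect.
- The trauma share is t_H in high-HDI and t_L in low-HDI centres, with t_L larger. If trauma were commoner in high-HDI centres, the bias would run the other way.
- The odds ratio (OR) for SSI, trauma against other cases, is 1.5, 2 or 3.
- Nothing else is adjusted for.

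Formulas:
- Trauma odds = OR × 0.10/0.90, and p1 = odds/(1 + odds). This gives p1 = 14.29%, 18.18% and 25.00% for OR 1.5, 2 and 3.
- Group risk = p0 + t × (p1 − p0).
- Spurious difference = (t_L − t_H) × (p1 − p0).
- Spurious HDI OR = [r_L/(1 − r_L)] / [r_H/(1 − r_H)], where r_L and r_H are the two group risks.

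| t_H, t_L | Trauma OR | r_H | r_L | Difference (points) | Spurious HDI OR |
|---|---|---|---|---|---|
| 1%, 3% | 1.5 | 10.04% | 10.13% | 0.09 | 1.01 |
| 1%, 3% | 2 | 10.08% | 10.25% | 0.16 | 1.02 |
| 1%, 3% | 3 | 10.15% | 10.45% | 0.30 | 1.03 |
| 1%, 5% | 1.5 | 10.04% | 10.21% | 0.17 | 1.02 |
| 1%, 5% | 2 | 10.08% | 10.41% | 0.33 | 1.04 |
| 1%, 5% | 3 | 10.15% | 10.75% | 0.60 | 1.07 |
| 2%, 10% | 1.5 | 10.09% | 10.43% | 0.34 | 1.04 |
| 2%, 10% | 2 | 10.16% | 10.82% | 0.65 | 1.07 |
| 2%, 10% | 3 | 10.30% | 11.50% | 1.20 | 1.13 |

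Worked example, last row: r_H = 0.10 + 0.02 × 0.15 = 0.103; r_L = 0.10 + 0.10 × 0.15 = 0.115; OR = (0.115/0.885)/(0.103/0.897) = 1.13.

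**Step 3. Compare with the effects the article reports.** The Introduction gives SSI rates from the first study of 7.4% in high-income and 20.0% in low-income countries, a gap of 12.6 points. The adjusted ORs against high-income countries were 1.96 (middle) and 2.06 (low). These are income groups rather than HDI groups, but they are the nearest benchmark. The largest spurious difference above, 1.20 points, is 1.20/12.6 = about 10% of that gap. As a rough check, 2.06/1.13 = 1.82, so even the extreme row would leave a substantial association. The power calculation works with a "minimum difference from 7% to 10% in SSI rate between two groups", that is, 3 points. Against that smaller contrast the range of 0.09 to 1.20 points counts for more, but the 3 points are a detectable difference, not the expected one.

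**The case against.** The strongest case on the other side has four parts.

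**It is not a contradiction.** Box 1 decides who enters the study and does not promise each indication its own code. Malignant or Benign can be read as cancer or not cancer, which covers everyone. Hernia repair with bowel resection is also named in Box 1 and has no indication code. The data set was kept minimal on purpose. This stands: the point is a gap in coding, not a conflict over eligibility. It does not remove the gap, because a further option in an existing field adds no data item.

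**A trauma code may exist elsewhere.** The operation drop-down is not reproduced, and the Quality of data section refers to a detailed protocol published online. This also stands. The point is therefore limited to the required fields as printed. Those fields do print the response options for indication, so this is more than detail left out of an article.

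**Adjustment is not impossible.** A reader might infer that trauma cannot be adjusted for at all. The documents do not support that. Urgency, contamination, ASA, approach and operation are all collected, and much of any excess risk may act through them. Only direct adjustment for trauma as a variable is lost.

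**The information may not be lost for good.** A reader might infer from the anonymous central database that trauma status could never be recovered. Table 1 starts with a local patient identifier, and the Investigators section makes a local investigator guarantor of each hospital's data. Sites might therefore trace their own cases, though that would be a retrospective query across many centres.

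**Conclusion.** The coding gap holds on the fields shown, and it is minor. Trauma is explicitly eligible, would be entered as Benign, and cannot be directly identified, described or adjusted for in the HDI model.

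Its effect on the estimate is unknown from the documents. The spurious OR of about 1.01 to 1.13 rests on assumed trauma shares and risks and is calculated before any other adjustment. The proxy variables should reduce it. Eligibility is confined to resections, cholecystectomy and appendicectomy, so trauma laparotomy without one of these is out, and the larger trauma shares in the table have no support in the text.

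The crude incidence of SSI, which is the primary outcome, is not affected. The strengths and limitations list already describes the HDI comparisons as hypothesis generating. It would be wrong to read this point as showing that the HDI result is invalid or that trauma could explain the gradient seen in the first study.

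**What to change.** Add Trauma as a third option of the existing indication field in REDCap, giving Malignant, Benign and Trauma. Use the three-level variable in the planned risk adjustment, report the number of trauma cases by HDI group, and repeat the HDI comparison without trauma cases as a sensitivity analysis. If the operation drop-down or the full online protocol already identifies trauma, say so in the article and use that item instead.

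The cost is one extra response option and one extra analysis. No field is added, so the rule requiring more than 95% complete data is no harder to meet. The trauma level may be sparse and its coefficient imprecise. If collection has already started, earlier cases would need a query to sites through their local identifiers. Given the likely size of the effect, that is worthwhile only if it is easy to do.

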**Antibiotic use**	
Used for treatment before surgery (eg, trial of antibiotics to treat diverticular abscess)	Yes (total days), No
Used for prophylaxis at the point of incision (ie, standard hospital prophylaxis)	Yes, No
Continued at the end of surgery (ie, extended prophylaxis after surgery)	Yes (total days), No
Was epidural analgesia inserted on the day of surgery?	Yes, No
Were NSAIDs used postoperatively during the first 5 days of after surgery? (including ibuprofen, naproxen, diclofenac, ketorolac and etoricoxib, excluding aspirin)	Yes, No
Was serum haemoglobin/haematocrit checked in the first 48 hours postoperatively?	Yes—serum haemoglobin, Yes—capillary PCV, No—but tests available in this centre, No—tests not available in this centre
Was serum creatinine checked in the first 48 hours postoperatively?	Yes, No—but available in this centre, No—not available in this centre
Length of postoperative stay	Days
**Surgical site infection**	
Prior to discharge	Yes, No
At 30 days after surgery	Yes, No, Not assessed after discharge
	*If yes:* Was a wound swab sent for microbiological culture: Yes, No—but available in this centre, No—not available in this centre
	*If yes:* How was this treated: operative drainage, wound opened outside of operating theatre, antibiotics (tick all that apply)
What bacteria, if any, were identified?	None, *Staphylococcus aureus*, Coliform, Anaerobe, Other (five tick boxes)
	*If yes*: Sensitivity: sensitive to antibiotic prophylaxis given; resistant to antibiotic prophylaxis given; sensitivities not tested—but available in this centre; sensitivities not tested—not available in this centre
30-day unexpected reintervention. Record the most serious reintervention	Yes—surgical, Yes—endoscopic, Yes—interventional radiology, No
30-day mortality	Dead, Alive, Unknown. *If died:* postoperative day of death
30-day intra-abdominal/pelvic abscess (CT, ultrasound or clinical (including reoperation) evidence of intra-abdominal or pelvic abscess)	Yes, No
Other hospital-acquired infection (treated with or without antibiotics)	Yes—urinary tract infection, Yes—pneumonia, Yes—central venous line infection, Yes—peripheral line infection, Yes—other, No
How was 30-day follow-up status achieved? (all applicable)	Still an inpatient, Clinic review, Telephone review, Community/home review, Discharged before 30 days and not contacted again

ASA, American Society of Anaesthesiologists; GI, gastrointestinal; NSAID, non-steroidal anti-inflammatory drug; PCV, packed cell volume.

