## Introduction

The burden of surgical disease in low and middle-income countries (LMICs) is growing.^1^ Specific programmes have aimed to highlight the unmet need for safe surgery and anaesthesia as part of the global health agenda.^2^ The Lancet Commission on Global Surgery outlined six core indicators for the assessment of global surgical systems, including the postoperative mortality rate (POMR).^3^ While clearly important, mortality only affects 1%–4% of all patients.^4^ For major gastrointestinal surgery, quantifying POMR alone neglects the burden of postoperative morbidity, which affects a greater proportion of patients.^2^ Other relevant markers of postoperative outcome are also needed to determine the success of surgery in the majority of patients who will survive.

Surgical site infection (SSI) is the most common complication following major gastrointestinal surgery,^5^ affecting between 25% and 40% of patients after midline laparotomy in high-income settings.^6 7^ SSI is implicated in one-third of postoperative deaths and accounts for 8% of all deaths caused by a nosocomial infection.^8–10^ Furthermore, SSIs cause pain and discomfort, increase hospital stay and put patients at greater risk of secondary infectious complications. This has an important economic impact with an attributable cost in the UK of £30 million per year.^11^

Our 2014/2015 prospective, observational cohort study (GlobalSurg 1^12^) included 10 475 patients from 58 countries. It showed that the incidence of SSI more than doubled from high (7.4%), to middle (14.4%), to low (20.0%)-income countries. This persisted after multivariable risk adjustment for patient and hospital confounders (middle income: OR 1.96 (1.63–2.32) and low income: OR 2.06 (1.67–2.57)). In the most contaminated procedures, one in three patients from LMICs suffered an SSI. Dirty surgery doubled in low-income countries (29.7% vs 16.6% in high-income settings), which was in turn associated with doubling of SSI (34.5% low income vs 15.4% high income). However, SSI was assessed as a secondary outcome measure as part of that study, lacking validity and requiring external validation.

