### Outcome measures

The primary outcome measure is the incidence of superficial or deep incisional SSI within 30 days of surgery involving any of the operative incisions made. This measure adopts the definitions within the 2008 Centre for Disease Control and Prevention^21^ definitions of SSI (box 2). Where it is unfeasible to follow-up the patients after discharge for 30 days postoperatively, in-hospital SSI incidence will be used as a proxy measure.Box 2Centre for Disease Control and Prevention (CDC) criteria for surgical site infection (SSI)^21^
CDC criteria for SSI require the patient to have at least one of the following:Purulent drainage from the superficial or deep (fascia or muscle) incision but not from within the organ/space component of the surgical siteAt least one of the following: pain or tenderness; localised swelling; redness; heat; fever and the incision is opened deliberately or spontaneously dehiscesAbscess within the wound (clinical, histopathological or radiological detection)

The secondary outcomes that will be derived from this study include:a description of the global variation in organisms causing SSI (including use of microbiological tests);the incidence of antibiotic-resistant pathogens detected in patients with SSI;30-day POMR;30-day postoperative reintervention rate;assessing how difference in SSI rates varies based on the method by which patients are followed up.

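### The follow-up-method field has no option for patients who die before day 30, which contaminates the secondary comparison of SSI rates by follow-up method

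*Protocol article*

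**What the plan says.** Outcome measures (protocol article) defines the primary outcome as the "incidence of superficial or deep incisional SSI within 30 days of surgery". Where follow-up after discharge is not feasible, "in-hospital SSI incidence will be used as a proxy measure". That rule addresses patients who went home; it does not mention patients who died. The same section lists, as a secondary outcome, how SSI rates differ by the way patients were followed up. Secondary aims states the same interest.

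Table 1, presented as the required data fields, fixes the codes:

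- SSI "Prior to discharge": yes or no.
- SSI at 30 days: "Yes, No, Not assessed after discharge".
- How 30-day status was obtained, with all applicable options to be ticked: "Still an inpatient, Clinic review, Telephone review, Community/home review, Discharged before 30 days and not contacted again".
- 30-day mortality: "Dead, Alive, Unknown", with the postoperative day of death if the patient died.

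The Introduction gives the only mortality figure, "mortality only affects 1%–4% of all patients", without a breakdown by HDI or income group.

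**The concern.** The follow-up-method field sorts patients into the groups of a planned comparison. A patient who dies on the ward on day 3 was not an inpatient at day 30, was not reviewed in clinic, by telephone or at home, and was not discharged. No option is true, so the site must tick an untrue one or none. A blank carries a penalty: Study setting excludes centres with more than 5% missing data and removes them from authorship. That favours ticking the nearest option, probably the inpatient one.

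The 30-day SSI field adds a second inconsistency. One site may enter 'No' for this patient, and another may choose the not-assessed code, although that code presupposes a discharge.

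At stake is whether differences in SSI rate between follow-up methods reflect how well each method finds infections, or partly where deaths were filed.

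**Working it through.** The article gives no figure on this point to reproduce. The check has three parts.

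**1. Two patient histories against the Table 1 codes**

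| Field | Dies in hospital, day 3, no SSI | Dies after discharge, before day 30, never contacted |
|---|---|---|
| SSI before discharge | No (true) | Yes or No (true) |
| SSI at 30 days | 'No' is true; the not-assessed code presupposes discharge | The not-assessed code fits |
| Follow-up method | None of the five fits | The last option fits, but mixes the dead with living patients who were not contacted |
| Mortality and day | Recorded | Recorded if known |

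The clear failure is the follow-up-method field for in-hospital deaths.

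**2. Follow-up-method comparison**

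Inputs: deaths m = 1% to 4% of patients (Introduction), and true day-30 inpatients i = 2% to 5% of patients (assumption; the article gives no figure). As the extreme case, suppose every death is entered under the inpatient option. The share of that category made up of deaths is s = m/(m + i).

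- Lowest: 1/(1 + 5) = 17%.
- Highest: 4/(4 + 2) = 67%.

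If true inpatients have SSI rate r and all these deaths were SSI-free, the category shows r × (1 − s), that is 0.83r down to 0.33r.

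The direction is not certain. The Introduction says SSI is implicated in one-third of postoperative deaths. If that meant that one-third of these patients had a recorded incisional SSI (an assumption), the category would show r(1 − s) + s/3, which is pulled towards one-third from either side.

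**3. Primary outcome**

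Let p be SSI cases divided by all patients, and d the share who die without SSI. Counting those deaths as non-events gives p. Excluding them gives p/(1 − d). Take p from the earlier cohort's income-group rates in the Introduction, and let d run from 1% to 4%, as if every death were SSI-free (the upper limit).

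- High income: 7.4/0.99 = 7.5%; 7.4/0.96 = 7.7%. Change 0.1 to 0.3 points.
- Low income: 20.0/0.99 = 20.2%; 20.0/0.96 = 20.8%. Change 0.2 to 0.8 points.
- Low-to-high risk ratio: 20.0/7.4 = 2.70 with all patients counted. With 4% deaths excluded in low-income and 1% in high-income settings (an assumed split), it is 20.83/7.47 = 2.79.

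A hypothetical rate had nobody died, giving the dead twice the survivors' risk, would be 20.0 + 0.04 × 2 × 20.83 = 21.7% in the low-income group, about 1.7 points higher. The article does not name that rate as its target.

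The two SSI codes need not change the result for an in-hospital death. If the in-hospital proxy is applied patient by patient, a death without SSI is a non-event under either code. If not-assessed patients were dropped instead, the rate would rise, as shown above.

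**The case against.** A reader might infer more: that early deaths have no valid SSI code at all, so SSI is understated, and most where mortality is highest. The documents do not support this, for three reasons.

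- 'No' is a true answer for a patient who died without an SSI, and the pre-discharge field can be completed for any in-hospital death.
- The defined outcome is incidence within 30 days of surgery. With death as a competing event, that cumulative incidence is SSI cases over all patients. Deaths without SSI belong in the denominator, and listing them separately leaves the SSI percentage unchanged.
- Mortality is given for all patients together, so any gradient in death across HDI groups is an assumption.

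The remaining defence is that death and day of death are collected, so an analyst can identify these patients, and that a condensed article leaves such handling to a fuller protocol or analysis plan that is not shown. This largely stands for the analysis, and it is why the point is minor. It does not remove the point. The option list is fixed in this article as a required field, and taken as written it puts deaths into follow-up groups to which they do not belong. Recovery from the mortality field also works only where the death is known.

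**Conclusion.** The point holds for the follow-up-method field and the secondary comparison built on it. In-hospital deaths before day 30 have no true option there, and sites may differ in the 30-day SSI code they choose. The possible distortion is concentrated in whichever category receives the deaths. The 17% to 67% share is an extreme illustration: it rests on an assumed 2% to 5% of true day-30 inpatients and on every death being entered there.

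The primary outcome is not understated. Even if all deaths were SSI-free, excluding them would move the rate by at most about 0.8 points at 20.0%, and the contrast between income groups would change little. Severity is minor.

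**What to change.** - Add a died-before-day-30 option to the follow-up-method field. If data are already collected, derive it from the recorded mortality and day of death.
- Leave those patients out of the comparison of SSI rates by follow-up method, and report how many were left out.
- Keep all patients in the primary SSI denominator, and show deaths without SSI as a separate row by HDI group.

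The cost is one extra drop-down option and one extra table row. No new data are needed.

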**Methods and analysis:**

This multicentre, international, prospective cohort study will be undertaken by any hospital providing emergency or elective gastroenterological surgical services. Centres will collect observational data on consecutive patients undergoing emergency or elective gastrointestinal resection, cholecystectomy or appendicectomy during a 6-month period. The primary outcome is the incidence of SSI with secondary outcomes describing the organisms causing SSIs, including their antibiotic susceptibility, and the microbiological tests used to identify them.

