### Secondary aims

The secondary aims include describing the organisms causing SSIs, the incidence of antibiotic-resistant pathogens and the microbiological tests used to identify them. The impact of the method of 30-day follow-up on these outcomes, where performed, will also be analysed.

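### The antibiotic-resistance outcome is broader than what the form measures: isolates are coded only against the prophylaxis given, and the prophylactic agent is never recorded

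*Protocol article*

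**What the plan says.** Three places in the protocol article promise a general description of resistance:

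- Secondary aims: "The secondary aims include describing the organisms causing SSIs, the incidence of antibiotic-resistant pathogens and the microbiological tests used to identify them".
- Outcome measures: "the incidence of antibiotic-resistant pathogens detected in patients with SSI".
- Abstract, Methods and analysis: "secondary outcomes describing the organisms causing SSIs, including their antibiotic susceptibility".

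None of them limits resistance to the prophylactic drug.

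Table 1 sets out the data behind these promises. Under Surgical site infection, the sensitivity field has four answers. Two carry a result: "sensitive to antibiotic prophylaxis given; resistant to antibiotic prophylaxis given". The other two mark the absence of one: "sensitivities not tested—but available in this centre; sensitivities not tested—not available in this centre". Under Antibiotic use, the prophylaxis item, "Used for prophylaxis at the point of incision (ie, standard hospital prophylaxis", is answered Yes or No. The item on extended prophylaxis, "Continued at the end of surgery (ie, extended prophylaxis after surgery", and the item on treatment before surgery are Yes (with total days) or No. None of the three asks for a drug or class.

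The section on statistical analysis says that variation in outcome across contexts will be tested by HDI.

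**The concern.** A resistance rate can be interpreted only if the reader knows which drug the organism resisted. Here the reference drug is the local prophylaxis and may differ from hospital to hospital. The same isolate could be entered as resistant in one centre and sensitive in another because the regimens differ. If choice of agent varies with HDI, a difference in recorded resistance between HDI groups may reflect prescribing, resistance or both.

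There is also a smaller gap. The prophylaxis item allows No, but the sensitivity field has no matching answer. An investigator with a tested isolate from such a patient must choose a code that does not fit or leave the field blank.

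What is at stake is the meaning of one secondary outcome. The primary outcome, SSI incidence, is not affected.

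**Working it through.** The plan gives no figure for resistance, so there is none to reproduce. The check sets the outcome against the fields and then illustrates the size under stated assumptions.

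**Step 1. Outcome against data fields.**

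| Needed for the stated outcome | Collected in Table 1 |
|---|---|
| Organism | Yes, in broad groups |
| Whether sensitivities were tested | Yes, with the reason if not |
| Resistance to a named drug or class | No; only relative to the prophylaxis given |
| Identity of the prophylaxis given | No; Yes/No only |
| A code for tested isolates without prophylaxis | No |

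**Step 2. Effect of choice of agent.** Assume two settings with identical flora, two agents A and B, and resistance r_A and r_B. Let w be the share of patients with a tested isolate who were given A.

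Recorded resistance = w × r_A + (1 − w) × r_B

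For r_A = 20% and r_B = 40%:

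- Setting 1, w = 80%: 0.80 × 0.20 + 0.20 × 0.40 = 0.24
- Setting 2, w = 20%: 0.20 × 0.20 + 0.80 × 0.40 = 0.36

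The gap is 12 points although the flora are the same. In general the gap is (w₁ − w₂) × (r_B − r_A):

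| r_A, r_B | A used in 60% vs 40% | 80% vs 20% | 90% vs 10% |
|---|---|---|---|
| 10%, 30% | 18% vs 22% (4 points) | 14% vs 26% (12) | 12% vs 28% (16) |
| 20%, 40% | 28% vs 32% (4) | 24% vs 36% (12) | 22% vs 38% (16) |
| 20%, 60% | 36% vs 44% (8) | 28% vs 52% (24) | 24% vs 56% (32) |

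All inputs in this table are assumptions. The range is 4 to 32 points. Because w is not collected, the distortion can be neither estimated nor removed.

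**Step 3. Patients without prophylaxis.** Assume recorded resistance of 30% among tested patients who had prophylaxis, and let u be the share of tested patients who had none. The recorded rate depends on how those patients are entered:

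- coded sensitive: 0.30 × (1 − u)
- left missing: 0.30
- coded resistant: 0.30 × (1 − u) + u

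For u = 10% this gives 27%, 30% or 37%. For u = 20% it gives 24%, 30% or 44%. The document does not say how many such patients to expect. That there may be some is inferred from the No option.

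**The case against.** The strongest reply is that the field measures something useful. Resistance to the local prophylaxis, among treated patients with a tested isolate, can be tabulated by HDI group. It bears on the effectiveness of prophylaxis worldwide, which the abstract names as unknown. This stands, and a claim that nothing could be compared across settings would go too far. But this measure is not the outcome that the article names.

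A second reply is that patients without prophylaxis can be found through the Yes/No item and excluded. This also stands, so that part is largely repairable in analysis. The missing agent is not.

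A third reply is that the outcome is descriptive, that HDI comparisons of incidence and risk factors are declared hypothesis-generating, and that the data set was kept short on purpose, with centres above 5% missing data excluded. These points limit the severity and give each added field a real cost. They do not make the label match the measure.

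A last reply is that an article condenses a fuller protocol. However, Table 1 is titled as the required fields, and the Data points section presents it as a minimal set built around the outcomes. An analysis plan cannot recover a drug that was not recorded.

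Two stronger readings are tempting and are not supported:

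- A reader might infer that untested infections count as non-resistant, so that settings with little testing look best. No section states such a denominator. The form codes untested isolates separately, and the swab item does the same: "Was a wound swab sent for microbiological culture: Yes, No—but available in this centre, No—not available in this centre".
- A reader might infer that a single sensitivity answer covers several ticked organisms. The table layout does not settle this; one answer per organism is an equally possible reading.

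**Conclusion.** The point holds in a limited form. The stated resistance outcome is broader than the data set behind it, because susceptibility is coded only against an unrecorded local agent and tested patients without prophylaxis have no fitting code. A difference between HDI groups would mix resistance with choice of agent and could not be adjusted for. Under the assumptions tried, identical flora can yield spurious gaps of 4 to 32 points. That range illustrates the mechanism; it does not predict this study's results. It assumes two agents and the same tested flora in both settings. The reading of the fields rests on the text alone and needs no assumption. The change should be made, but it concerns a secondary outcome and does not threaten the main result.

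**What to change.** If the form can still be changed, add one drop-down for prophylactic agent or class, shown when prophylaxis is Yes, and add a code for no prophylaxis given to the sensitivity field. Resistance can then be compared between HDI groups within the same agent or class. The cost is one or two short fields, which also count towards each centre's completeness threshold.

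If the form cannot be changed:

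- Rename the outcome 'resistance of cultured SSI organisms to the prophylaxis given'.
- Take as denominator SSI patients who had prophylaxis and have a sensitivity result.
- Show swab and sensitivity-testing rates by HDI group beside it. Use of microbiological tests is already an aim, so only the breakdown is new.
- Do not report the result under the present, general label.

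This second route costs only wording and a smaller denominator. It leaves choice of agent and resistance mixed, and the report should say so.
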